### Study Population

Patients are eligible for participation in this study if they are 18 years of age or older, have documented AF, are scheduled for an AF ablation (first procedure or redo) in either participating center, and are able and willing to provide written informed consent. There are no restrictions for AF ablation modality nor for potential previous ablation procedures. Possible ablation modalities include percutaneous techniques (cryoballoon ablation or radiofrequency ablation), surgical ablations (epicardial ablation, concomitant ablation) or a combined procedure (hybrid ablation). Patients are excluded if they are deemed unfit to participate due to a serious medical condition or if they undergo an emergency procedure. In- and exclusion criteria are listed in Table 1.

**TABLE 1 T1:** In- and exclusion criteria of the ISOLATION study.

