#### Development of Prediction Model and Sample Size Calculation

An exploratory multimodality model will be created to predict the primary endpoint (ablation success). Ideally, to develop a reliable prediction model all variables of interest that will be studied in the model should be defined prior to the data collection. However, this study includes several relatively new techniques, which each provide a multitude of possible variables of interest for which the predictive value has not been established. Defining variables to be included in the model up-front could limit its eventual predictive value, as the predefined variables might not prove to be the most discriminative variables. Therefore, an exploratory analysis of variables in the following categories will be performed first (Figure 1): (1) clinical risk factors, (2) pre-procedural AF patterns, (3) anatomical characteristics, (4) electrophysiological characteristics, (5) circulating biomarkers, and (6) genetic background. For subcategory 1–5 the three variables with the strongest correlation to ablation success are selected and presented to the model. For subcategory 6 the two strongest predictors are used. The ablation technique that is chosen is used as a separate predictor. This approach leads to a total of 18 variables used to develop the multimodality model. To ensure sufficient power to explore these 18 variables, a total of 180 events is required to conform to the rule-of-thumb to aim for 10 events per variable. When assuming an event rate of 32% (68% successful AF ablations) (4, 5), inclusion of 563 patients is required to achieve sufficient events. Accounting for a lost-to-follow-up rate of 15%, the aim is to include 650 patients scheduled for first catheter ablation.

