Variables with possible interrelation (e.g., left atrial volume index or AF type with chosen ablation technique) will be tested for interaction and, if present, interaction terms will be included in the model. The model will be developed using logistic regression by forward selection with the use of the Akaike Information Criterion (AIC) as stopping rule. The discriminative performance of the model is evaluated by calculating the area under the receiver operator characteristic (AUROC) curve (C-statistic) and by comparisons of observed groups of different predictive frequencies. To assess the potential confounding effect of the ablation strategy that was chosen, performance analyses will be done for the entire cohort and separately for patients treated with different ablation strategies for sensitivity purposes.

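### The ten-events-per-variable claim counts only the 18 variables left after an outcome-based screen in the same data, so it does not support sufficiency for the model-building process described

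*Protocol article*

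**What the plan says.** All of this is in the protocol article, mostly under Development of Prediction Model and Sample Size Calculation.

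- **Screening.** An exploratory analysis in six domains comes first. "For subcategory 1–5 the three variables with the strongest correlation to ablation success are selected and presented to the model". For genetics, "For subcategory 6 the two strongest predictors are used". The section explains that the newer techniques each yield many possible variables of unproven value. It concedes that defining the variables beforehand would be ideal.
- **Technique.** "The ablation technique that is chosen is used as a separate predictor". It is counted as one variable. Under Study Population: "Possible ablation modalities include percutaneous techniques (cryoballoon ablation or radiofrequency ablation), surgical ablations (epicardial ablation, concomitant ablation) or a combined procedure (hybrid ablation)".
- **Count and size.** "This approach leads to a total of 18 variables used to develop the multimodality model". Then: "To ensure sufficient power to explore these 18 variables, a total of 180 events is required to conform to the rule-of-thumb" of ten events per variable. A 32% event rate gives 563 patients, and 15% loss to follow-up gives 650.
- **After the count.** Variables that may be interrelated, such as left atrial volume index or AF type with technique, "will be tested for interaction and, if present, interaction terms will be included in the model". The model is then built by forward selection with AIC as the stopping rule.

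**The concern.** An events-per-variable rule guards against overfitting. It does so only if the denominator includes every parameter that the outcome had a chance to pick. Here the outcome has filled 17 of the 18 places before the rule is applied, and forward AIC selection then searches the same data again. Variables that win such a contest tend to have inflated coefficients, and the rule as applied does not see this.

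The rule is also not a power calculation. The article states no effect size and no power, so the word power has no basis in that sense either.

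This statement is the only justification given for 650 patients. The section evaluates the model by AUROC and by comparing observed groups. If these are computed on the data that chose the variables, optimism from the screen would look like good performance. The Conclusion expects the predictors to help tailor treatment decisions to individual patients.

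**Working it through.** **Inputs from the article:** 3 variables in each of five domains, 2 from genetics, 1 for technique; 10 events per variable; event rate 32%; loss to follow-up 15%; planned size 650; recurrence of 30-50% quoted in the Introduction. **Not given:** the number of candidates screened, the coding of technique, and the correlation among candidates within a domain.

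**1. The plan's own figure.**
- Variables: 5 x 3 + 2 + 1 = 18. Events: 18 x 10 = 180.
- Evaluable patients: 180 / 0.32 = 562.5, so 563.
- Enrolled: 563 / 0.85 gives 663; 563 x 1.15 gives 648. The stated 650 agrees with these to within 3%.

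The arithmetic reproduces. The question is what was counted.

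**2. Events expected at 650.** 650 x 0.85 = 552.5 evaluable; 552.5 x 0.32 = 176.8 events, about 177. Over 18 terms: 176.8 / 18 = 9.8.

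**3. Technique coding (not stated).**
- 1 parameter: 18 in total, 9.8 events each.
- 2 parameters (three levels): 19 in total, 176.8 / 19 = 9.3.
- 4 parameters (five levels): 21 in total, 176.8 / 21 = 8.4.
- At a 40% event rate: 552.5 x 0.40 = 221 events, and 221 / 21 = 10.5, so this shortfall disappears.

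**4. Counting the candidates screened (pool sizes are assumptions).**

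| Candidate parameters | Events per parameter at 32% |
|---|---|
| 50 | 176.8 / 50 = 3.5 |
| 60 | 176.8 / 60 = 2.9 |
| 100 | 176.8 / 100 = 1.8 |
| 120 | 176.8 / 120 = 1.5 |

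At a 50% event rate, 552.5 x 0.50 = 276 events, and 276 / 50 = 5.5. The top of the quoted recurrence range does not restore ten per parameter for a pool of 50.

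**5. Does screening matter in practice?** Two kinds of simulation used the described process: top three per domain and top two in genetics, followed by forward AIC.

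- *Pure noise* (n = 563, 32% events, independent predictors, 100 runs; true AUROC 0.50). Mean apparent AUROC was 0.58 with 18 prespecified predictors. It was 0.64, 0.69 and 0.72 when the screened slots were filled from 10, 20 and 50 candidates per domain.
- *Four true predictors* (n = 552, 32% events; an AUROC of 0.66 attainable if the true model were known). Calibration slope in validation data:

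| Candidates per domain | Independent | Correlation 0.5 within domain | Correlation 0.7 within domain |
|---|---|---|---|
| No screening | about 0.75 | 0.76 | not run |
| 10 | about 0.50 | 0.64 | 0.70 |
| 20 | about 0.41 | 0.57 | not run |

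The direction is the same throughout, but the size depends heavily on the assumed correlation. A slope of about 0.75 without any screening shows that part of the shrinkage is unrelated to the screen.

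**The case against.** The best defence is candour. The article calls the model exploratory, says that prespecification would be better and explains why it was not done. The sufficiency sentence refers only to exploring the 18 variables. That justifies the screening. It does not justify the claim, because those 18 exist only as a result of the screen and no other basis for the size is offered.

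A second defence is that the candidate list may sit in the analysis plan. It may, and its absence from an article is no fault. But the article itself fixes the count, the rule, the screen and the selection method, and asserts sufficiency.

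Four stronger readings are tempting and are not supported:

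- *Technique is miscounted as one parameter instead of four.* The article lists modalities but does not say how they will be coded. The section on the ablation procedure groups some of them together. The sample size paragraph describes the 650 as first catheter ablations, which could leave only cryoballoon against radiofrequency (one parameter), although Study Population also admits redo and surgical procedures.
- *Interactions bring the total to 29 parameters and 6.1 events each.* This needs two interactions, both retained, each with four parameters. The article adds interactions only if they are found.
- *The final model will be badly overfitted, with a slope near 0.5.* That figure needs independent candidates and about ten per domain. Shrinkage or optimism correction may also be in the analysis plan, which is not shown.
- *177 events falls short of 180.* The gap is within rounding and is not a separate error.

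**Conclusion.** The point holds: the statement that 180 events ensures sufficient power is not supported for the process described, because the rule is applied after the outcome has chosen 17 of the 18 variables. The direction is certain, since the pool must be larger than the places it fills for selection to mean anything. The size is not certain. It is about 3.5 to 1.5 events per candidate for assumed pools of 50 to 120 at a 32% event rate, against the 9.8 obtained from the 18 alone. The technique part is minor, depends on unstated coding and vanishes at a 40% event rate.

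A reader might infer that the study is too small and must enrol more. That does not follow. Ten events for each of 50 candidates would need 500 events, 500 / 0.32 = 1,563 evaluable and 1,563 / 0.85 = 1,839 enrolled. An exploratory cohort need not meet that if it describes its size correctly and corrects its performance estimates. This should be fixed, but it does not invalidate the study.

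**What to change.** 1. Withdraw the statement that 180 events gives sufficient power for the model.
2. Report the expected events (about 177) against the total number of candidate parameters screened, including technique levels and interaction terms.
3. Where possible, shorten each domain's list without looking at the outcome, for example by redundancy, missingness or measurement quality.
4. Name the technique levels and the allowed interactions in advance.
5. Repeat the whole process (domain screening, interaction testing and forward AIC) within each bootstrap sample. Report optimism-corrected AUROC and calibration, and shrink the coefficients accordingly.

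This keeps the selection by domain, which suits the article's wish for a small number of additional modalities. A single penalised logistic model over all remaining candidates is an acceptable alternative, not a requirement.

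The cost is revised wording, somewhat more analysis and a less favourable events-per-variable figure. No extra enrolment or data collection is needed.

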### Statistical Considerations

Data analyses will be performed with SPSS Statistics, version 25.0 or higher (IBM SPSS Inc., Chicago IL). Baseline data will be presented by count (percentage) for categorical variables and compared using the Chi-square test. Continuous data will be presented as means (± standard deviation) or medians (interquartile range) and compared using the independent samples *t*-test or Mann-Whitney *U*-test. Missing data will be estimated using multiple imputation by chained equations. Uni- and multivariable regression analyses will be performed to analyze the relation of dependent variables with the primary and applicable secondary endpoints. The secondary endpoints time to recurrence of atrial arrhythmia and AF will be assessed using Cox proportional hazard regression. All endpoints will be assessed using a level of significance of α = 0.05.

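### With 15% loss to follow-up, 650 patients fall slightly short of the plan's own 563 patients and 180 events; the sample size sentence should be restated

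*Protocol article*

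**What the plan says.** Everything needed is in the protocol article, under *Development of Prediction Model and Sample Size Calculation*. Three variables from each of five domains, two from the genetic domain and the ablation technique make up the candidate set: "This approach leads to a total of 18 variables used to develop the multimodality model". The event target follows from that count: "a total of 180 events is required to conform to the rule-of-thumb to aim for 10 events per variable". With an assumed event rate of 32%, the article states that "inclusion of 563 patients is required to achieve sufficient events". It then allows for attrition: "Accounting for a lost-to-follow-up rate of 15%, the aim is to include 650 patients scheduled for first catheter ablation".

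The Abstract, *Study Design* and *Current Study Status* repeat the target of 650 without further derivation. The article does not say how the 15% was applied to the 563.

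**The concern.** An allowance for loss to follow-up should leave the required number after the loss has occurred. If a fraction d of those enrolled is lost, enrolment must be n/(1 - d). Multiplying by (1 + d) gives a smaller number, because d is then taken as a share of the required patients and not of the enrolled ones. The step from 563 to 650 looks like the second calculation.

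What is at stake is whether the sentence is accurate. The events-per-variable target is the only sample size criterion that the article gives, and it presents 650 as meeting that target after 15% loss. A reader who relies on the sentence will believe that 10 events per variable are secured under the stated assumptions, when the same assumptions give slightly fewer.

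**Working it through.** **Inputs**, all from *Development of Prediction Model and Sample Size Calculation*: 18 variables, 10 events per variable, event rate 32%, loss to follow-up 15%, planned enrolment 650. Significance level, power and effect size do not enter this calculation.

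**Reproducing the plan's figures**

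- Variables: 3 x 5 + 2 + 1 = 18. Matches.
- Events: 18 x 10 = 180. Matches.
- Patients before loss: 180 / 0.32 = 562.5, rounded up to 563. Matches.
- Enrolment by multiplication: 563 x 1.15 = 647.45, so 648. Rounding up further gives the stated 650.
- Enrolment by division: 563 / 0.85 = 662.35, so 663. This lies above 650, so rounding up cannot turn it into 650.

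**What 650 delivers at 15% loss**

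- Evaluable patients: 650 x 0.85 = 552.5, which is 10.5 below 563.
- Events: 552.5 x 0.32 = 176.8, which is 3.2 below 180.
- Events per variable: 176.8 / 18 = 9.82.

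**What would satisfy the stated requirement**

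- Enrolment at 15% loss: 663. Check: 663 x 0.85 = 563.55 patients, and 563.55 x 0.32 = 180.3 events. The difference from 650 is 13 patients, or 13 / 650 = 2.0%.
- Largest loss that 650 can absorb: 1 - 563/650 = 13.4%.
- Event rate at which 650 with 15% loss reaches 180 events: 180 / 552.5 = 32.6%.

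**Sensitivity to the event rate**, with 650 enrolled and 15% lost, over the 30-50% recurrence range given in the Abstract and Introduction:

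| Event rate | Events | Events per variable |
|---|---|---|
| 30% | 166 | 9.2 |
| 32% (plan) | 177 | 9.8 |
| 35% | 193 | 10.7 |
| 40% | 221 | 12.3 |
| 50% | 276 | 15.3 |

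**The case against.** The strongest case on the other side is that the gap has no practical consequence. Ten events per variable is described as a rule of thumb, the model is described as exploratory, and no test or decision depends on reaching exactly 180. The difference between 9.8 and 10 does not change how reliable the model will be. This stands, and it sets the size of the point.

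A second objection is that lost patients are not wholly lost. Under *Statistical Considerations* the article states: "Missing data will be estimated using multiple imputation by chained equations". It does not say whether outcomes are included. Even if they are, imputation adds no observed events, and the 15% allowance itself treats these patients as lost. It is also true that a patient whose recurrence was documented before loss has already supplied an event. At the plan's rate, the 97.5 lost patients correspond to 97.5 x 0.32 = 31.2 events, so recovering about a tenth of them (3.2 / 31.2) would close the gap. The article makes no such assumption. This softens the shortfall in practice but does not make the sentence correct.

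Three stronger readings are tempting, and the document does not support them:

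- *The sponsor multiplied by 1.15.* A reader may infer this, and the numbers fit it well, but no formula is stated. The discrepancy does not depend on it: however 650 was obtained, it does not cover 15% loss.
- *The study is underpowered.* A shortfall of about 3 events in 180 does not show that.
- *There is no reserve, because recurrence may be as low as 30%.* The cited range runs to 50%, and 180 events are reached from about 32.6%, so most of the range meets the target. A low event rate is also a separate matter from the loss allowance: 663 patients at 30% would give 663 x 0.85 x 0.30 = 169 events and miss the target too.

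**Conclusion.** The point holds as a small arithmetic inconsistency. On the article's own inputs, 650 patients with 15% loss give about 552 evaluable patients and about 177 events (9.8 per variable), where the text requires 563 and 180. The stated allowance would need 663. Nothing elsewhere in the article reconciles the figures.

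This rests on two readings: that the 15% is a share of the patients enrolled, and that a lost patient contributes no event. The first is the ordinary meaning of a loss to follow-up rate; the second is what making an allowance implies. The correction is worth making because the sentence is wrong as it stands and costs almost nothing to put right. The consequences for the study are slight.

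**What to change.** Keep the target of 650 and restate the one sentence in *Development of Prediction Model and Sample Size Calculation*, in either of two ways:

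- State that 650 patients cover a loss to follow-up of about 13%. Check: 650 x 0.87 = 565.5 patients and, at 32%, 181 events.
- Keep the 15% and state that about 177 events are then expected, or 9.8 per variable.

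The cost is one sentence and a slightly less favourable figure. No other section changes, because 650 remains the target throughout. Raising enrolment to 663 would also make the sentence true but is not needed for a gap of this size. Cutting the candidate set to 17 variables (176.8 / 17 = 10.4 per variable) is not advised: it would change the design to make up about 3 events.

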## Introduction

The prevalence of atrial fibrillation (AF) has risen substantially over the past decade, and it continues to rise due to the aging population and the increasing rate of concomitant risk factors and underlying structural heart diseases (1). AF is associated with an increased risk of ischemic stroke, developing and worsening of heart failure, and a significant symptom and financial burden (2). To maintain sinus rhythm and to decrease symptoms related to AF, catheter ablation is recommended in symptomatic patients (3). However, despite advanced ablation techniques and improved ablation outcomes over the last decade, about 30–50% of patients still experience recurrences of atrial arrhythmias within 1 year after the procedure (4, 5).

Although several readily available characteristics (including demographic information, established clinical AF risk factors, and left atrial volume) have previously been identified as predictors for AF ablation success, it remains challenging to estimate the success rate for an individual patient (6). A range of novel techniques estimating the extent of the atrial AF substrate has been proposed: to aid in the prediction of individual success rates biomarkers, such as inflammatory mediators and markers for fibrosis (7, 8), common gene variants associated with AF, and non-invasive electrophysiological characteristics recorded on surface electrocardiograms (ECG) (9, 10). Additionally, a more detailed characterization of different AF patterns based on frequency, duration, and manner of conversion of AF episodes might further help to characterize the AF phenotype, although its predictive value for ablation success has not yet been described (11).

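### Outcome-based shortlisting followed by ordinary logistic regression, with no shrinkage step stated, will tend to give predicted success probabilities that are too extreme

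*Protocol article*

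**What the plan says.** All of the modelling plan is in the protocol article, section Development of Prediction Model and Sample Size Calculation.

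- **Candidate pool.** The newer techniques "each provide a multitude of possible variables of interest for which the predictive value has not been established". No number is given.
- **Shortlist.** "For subcategory 1–5 the three variables with the strongest correlation to ablation success are selected and presented to the model". For genetics, "For subcategory 6 the two strongest predictors are used". In addition, "The ablation technique that is chosen is used as a separate predictor".
- **Count.** "This approach leads to a total of 18 variables used to develop the multimodality model". Interaction terms are added where testing finds them.
- **Fit.** "The model will be developed using logistic regression by forward selection with the use of the Akaike Information Criterion (AIC) as stopping rule".
- **Performance.** "The discriminative performance of the model is evaluated by calculating the area under the receiver operator characteristic (AUROC) curve (C-statistic"), together with a comparison of observed groups at different predicted frequencies. Both are repeated by ablation strategy.

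The section calls the model exploratory. The Introduction describes the gap it addresses: "it remains challenging to estimate the success rate for an individual patient". The Conclusion foresees using the predictors to tailor treatment to the individual patient.

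**The concern.** Ranking variables on the outcome favours those whose association happens to be over-estimated in this sample. Forward AIC selection among the survivors repeats that choice on the same data. Maximum-likelihood coefficients estimated afterwards are too large on average, so the linear predictor is stretched and the calibration slope in new patients is expected to fall below 1.

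The stated performance measures are poorly placed to reveal this. The AUROC depends only on the ordering of patients and does not change when every linear predictor is stretched by a common factor. In the fitting data, the overall calibration slope of a maximum-likelihood logistic model is 1 by construction, so observed and predicted risk groups will look well aligned there.

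At stake are the absolute probabilities for patients at the two ends of the risk range. If the model is used for individual decisions, those are the predictions most likely to influence one. The issue is separate from optimism in the AUROC: correcting the AUROC would leave the coefficients unchanged.

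**Working it through.** **1. The plan's own figures.** Variables: 5 × 3 + 2 + 1 = 18. Events: 18 × 10 = 180. Patients: 180 / 0.32 = 562.5, rounded up to 563. Inflation for 15% loss gives 563 / 0.85 = 663, or 563 × 1.15 = 648; the stated 650 is close to both. The figures reproduce. With 650 enrolled and 15% lost, 650 × 0.85 = 552.5 patients and 552.5 × 0.32 = 176.8 events remain, or 176.8 / 18 = 9.8 events per variable. That ratio counts only the 18 shortlisted variables. It leaves out the variables screened, any extra ablation-technique categories and the interaction terms.

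**2. Expected slope without any screening.** Inputs: n = 552, 18 parameters, 32% events; R2 is assumed.

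- Maximum Cox-Snell R2 = 1 − exp{2[0.32 ln 0.32 + 0.68 ln 0.68]} = 0.715.
- LR = −552 × ln(1 − R2 Cox-Snell). With R2 taken as the true value, expected slope = LR / (LR + 18).
- Nagelkerke 0.10: Cox-Snell 0.0715, LR = 40.9, slope = 40.9 / 58.9 = 0.69.
- Nagelkerke 0.25: Cox-Snell 0.179, LR = 108.6, slope = 108.6 / 126.6 = 0.86.

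The alternative formula, 1 − 18 / LR, gives 0.56 and 0.83. It applies when R2 is the apparent, already optimistic value, so the first pair is the one to use here.

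**3. Simulation of the stated procedure.** Assumptions: 32% events, continuous candidates, top 3/3/3/3/3/2 by correlation with the outcome plus technique, then forward AIC logistic regression. The slope is measured in new patients. The table shows mean slopes for n = 563, independent candidates, one true predictor per domain plus technique, 120 runs per cell.

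| Candidates per domain | log OR 0.15 per SD | 0.25 | 0.40 |
|---|---|---|---|
| 3 (almost no screening) | 0.51 | 0.75 | 0.86 |
| 10 | 0.27 | 0.53 | 0.73 |
| 20 | 0.18 | 0.42 | 0.64 |

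In each of these cells, 90–100% of runs had a slope below 1. A second set of 24 scenarios used two true predictors per domain, 3 to 20 candidates, the same effect sizes, and within-domain correlation of 0 or 0.5. Mean slopes ran from 0.26 to 0.89, below 1 in 87–100% of runs. Correlated candidates or stronger effects mostly gave 0.67 to 0.89.

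**4. What a slope means for a patient.** Around the assumed mean success of 68% (logit 0.754), calibrated logit = 0.754 + slope × (predicted logit − 0.754). Predicted 90% has logit 2.197; predicted 40% has logit −0.405.

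| Slope | Predicted 90% becomes | Predicted 40% becomes |
|---|---|---|
| 0.9 | 89% | 43% |
| 0.53 | 82% | 53% |
| 0.3 | 77% | 60% |

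For example, at 0.53: 0.754 + 0.53 × 1.443 = 1.519, which is 82%.

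**The case against.** **The article does not exclude shrinkage.** It names a selection method and performance measures, and an analysis plan that is not shown could add post-fit shrinkage. This stands in part. A reader might infer that the coefficients will definitely be left unshrunk, but that would be reading silence as a decision. What remains is that the article does fix the shortlisting, the fitting method, the stopping rule and the performance measures, and that this procedure, followed as written, gives an expected slope below 1.

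**The model is exploratory.** The article says so, concedes that a reliable model would ideally predefine its variables, and words later uses conditionally. It does not promise a published equation or risk calculator. This softens the consequence. It does not remove it, because individual prediction is the stated gap and individual treatment decisions the foreseen use.

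**Observed frequencies in predicted groups are planned, also by ablation strategy.** This is fair credit: maximum likelihood does not force agreement in every risk group or stratum. But if these checks use the development patients, and no others are mentioned, they can hide overall stretching.

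**The size is driven by assumptions.** This stands. A reader might take a single scenario, say a slope near 0.5, as the error in this plan. The document gives no candidate counts, correlations or effect sizes, and stronger or correlated predictors bring the slope much closer to 1. Nor do the figures show that extreme-risk patients are really average: in most scenarios the high- and low-risk groups stay distinct, with predictions too far apart.

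**Conclusion.** The point holds as to direction. Outcome-based shortlisting, then forward AIC selection and an ordinary logistic fit in the same roughly 552 patients, gives an expected calibration slope below 1 in new patients. This is a tendency, not a certainty for one data set: up to 13% of runs in a scenario had a slope of 1 or more.

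The size is a range. The slope is about 0.3 to 0.9 with two true predictors per domain, 3 to 20 candidates, log odds ratio 0.15 to 0.40 per SD and within-domain correlation 0 or 0.5. It can be lower still (0.18) with 20 independent candidates and one weak true predictor per domain. With no screening and all 18 parameters kept, it is 0.69 to 0.86 for a true Nagelkerke R2 of 0.10 to 0.25. Ten events per variable does not remove the problem. For an exploratory model this is a cheap improvement and not a flaw that invalidates the study.

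**What to change.** Keep the stated selection and add one step before the model is reported:

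1. Draw bootstrap samples and repeat the whole procedure in each: ranking within domains, interaction testing, AIC selection and fit.
2. Apply each bootstrap model to the original cohort and average the calibration slopes.
3. Multiply the final coefficients by that average slope and re-estimate the intercept.
4. Report the optimism-corrected calibration slope and intercept beside the AUROC.

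The ranking must be inside the resampling. A bootstrap that starts from the 18 shortlisted variables would miss the part of the problem that comes from screening. This requires recording every variable screened.

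The cost is analysis code only, possibly outside SPSS, the package the article names. No patients, visits or measurements are added. The downside is that predicted risks are less spread out and look less decisive.
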